### Study design

To test our hypotheses, we will conduct a randomized controlled trial applying a 2 (SAR vs. control) x 2 (WE vs. control) between-subjects design. Participants will be stratified according to gender and randomly assigned to one of four conditions: (1) SAR only, (2) WE only, (3) SAR and WE, (4) no intervention (see Fig. 1). Participants will be blinded to their condition and will not be informed about the various interventions. Raters of the BBN-skills performance will receive video recordings of the BBN situations in a random order with no information about the assigned condition. SPs interacting with the participants will only be present for the BBN situation and will not be informed about which intervention was applied before the encounter. The experimenters will not be blinded, as they are required to set up the corresponding learning modules (including interventions) for each session.

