Upon arrival at the lab, the experimental session, the cardiovascular measurement instruments, and the saliva sampling procedure will be explained to the participants, and written consent will be obtained from them. When explaining the experimental session, the experimenter will specifically mention that the BBN task will be video recorded, based on which participants’ performance will be rated. This information aims to increase participants’ task engagement. After these explanations, participants will have to verify their compliance with the behavioral instructions (food intake, caffeine consumption, etc.). Any violation of the behavioral instructions will be noted and considered in the statistical analysis. Participants will then be fitted with the sensors of the cardiovascular measurement devices (Finometer and VU-AMS). Next, a first saliva sample (S1) will be collected and a questionnaire (Q1; see Fig. 2 for details) answered, followed by a cardiovascular baseline measurement of 5 min (CV1). After the baseline measurement, participants will be informed about the setting of the upcoming task (i.e., BBN in prenatal setting). This will be followed by a cardiovascular recording of 2 min (CV2), a second saliva sample (S2), and a second questionnaire (Q2). During the next 40 min, participants will learn how to BBN with a web-based tool that includes a short introduction to BBN and the SPIKES protocol [1]. This protocol divides BBN into six stages (i.e., Setting, Perception, Invitation, Knowledge, Emotion, Strategy & Summary). The assigned intervention (SAR and/or WE) or control material will be part of this learning module. Immediately after the learning period, another saliva sample will be collected (S3), and a third questionnaire will be answered (Q3). Participants will then receive detailed information about a diagnosis (Trisomy 21) and be given 5 more minutes to prepare, before they have to deliver the bad news to an SP. For the BBN task, participants will be given a time limit of 12 min but will be allowed to finish earlier. Cardiovascular data will be recorded for 2 min before (CV3), during (CV4), and for 2 min after the BBN task (CV5). Next, another saliva sample will be collected (S4), and a fourth questionnaire will be answered (Q4). For the remainder of the experiment, there will be two blocks consisting in cardiovascular recording (CV6, CV7), followed by questionnaires (Q5, Q6) and saliva samples (S5, S6). During the cardiovascular recordings (excluding the BBN task), participants will be asked to sit quietly in an upright position, to not cross their legs, keep their eyes open, and their hands on the table.

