### Stress arousal reappraisal

The content of the stress arousal reappraisal intervention is adapted from previous research [47, 61, 62, 69, 87, 99] and presented in the form of a 7-minute screencast using illustrations and voice-over. The screencast states that experiencing stress arousal is normal and legitimate and shows that an individual cares about a challenging situation. More specifically, participants will learn how stress arousal fulfills a vital function (e.g., an increased heart rate provides more oxygen to where it is needed) and is necessary for individuals to perform at their best. Therefore, stress arousal should be perceived as functional and beneficial for performance rather than harmful. To endorse the presented information, participants will then be asked to reflect on past and future stressful situations. Finally, right before the BBN communication task, participants will be reminded to reappraise the stress arousal they might experience in the encounter as beneficial for their BBN performance.

In the corresponding control condition, participants will be shown a 7-minute screencast about psychological and neurological learning processes (this is similar to control materials successfully used in previous studies, e.g., [87]).

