### Sample size calculation

An a-priori power analysis was performed to calculate the required sample size, using the G*Power 3 program [102]. We reviewed published data on psychophysiological and performance effects of our two interventions, to determine that an effect size of *d* = 0.40 [103] is scientifically reasonable and practically relevant. Given an alpha level of 0.05 (two-tailed) and a targeted power level of 0.80, *n* = 50 participants per group will be required. Thus, we will need a total of *N* = 200 participants with valid data to test our hypotheses. In case of device malfunctioning, dropouts, non-compliance or unusable data, additional participants will be scheduled until a total of 200 valid cases is reached.

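### Setting up a web-based learning module does not by itself require unblinded experimenters; the session after the learning phase and case-validity decisions should be shielded from knowledge of the arm

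*Protocol article*

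**What the plan says.** On experimenters, the Study design section is explicit: "The experimenters will not be blinded, as they are required to set up the corresponding learning modules (including interventions) for each session". The same section keeps three other groups unaware of condition: the participants, the simulated patients (SPs) and the raters who score the videos.

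The Experimental session section describes how the teaching is delivered: "participants will learn how to BBN with a web-based tool that includes a short introduction to BBN and the SPIKES protocol". It adds: "The assigned intervention (SAR and/or WE) or control material will be part of this learning module". The sections on the two interventions describe that material as a 7-minute screencast with a 7-minute control screencast, and a 10-minute video set against 10 more minutes with the written protocol. Timing is the same in every condition.

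One SAR element comes later: "right before the BBN communication task, participants will be reminded to reappraise the stress arousal they might experience". How this reminder is delivered is not stated.

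The Sample size calculation section sets the replacement rule: "In case of device malfunctioning, dropouts, non-compliance or unusable data, additional participants will be scheduled until a total of 200 valid cases is reached".

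**The concern.** The plan accepts unblinded experimenters for one practical reason, and that reason is weak for material delivered through a web tool. Nothing described in the 40-minute module needs a person who knows the arm.

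The hypotheses at stake are H1.1 and H2.1, on the resources-demands differential, the cardiovascular index, the anabolic balance and salivary alpha-amylase. Objective instruments prevent biased scoring. They do not prevent a real difference in arousal if staff are warmer, more encouraging or more tense with one arm. The article itself treats staff words as active: "When explaining the experimental session, the experimenter will specifically mention that the BBN task will be video recorded", and it gives raising task engagement as the purpose.

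The second route is selection. Cases judged unusable are replaced, and the article names no safeguard that this judgement is made without knowledge of the arm.

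**Working it through.** **1. What lies before and after the learning phase (Experimental session; Fig. 2 note)**

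| | Before learning | After learning |
|---|---|---|
| Cardiovascular recordings | CV1, CV2 | CV3 to CV7 (five; CV4 is the task with the SP) |
| Saliva samples | S1, S2 | S3 to S6 (four) |
| Questionnaires | Q1, Q2 | Q3 to Q6 (four; demands and resources in Q3 and Q4) |

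Only the right-hand column can carry an effect of staff reacting to the intervention a participant has received.

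**2. Who does what**

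- Explaining the session: the experimenter, before the learning phase.
- Fitting sensors: not stated. The text is in the passive: "Participants will then be fitted with the sensors of the cardiovascular measurement devices (Finometer and VU-AMS".
- Saliva sampling, recordings and questionnaires after learning: not stated.
- SAR reminder: not stated.
- Processing of cardiovascular recordings: software is named, but not the operator.
- Deciding that a case is unusable: not stated.
- Checking food, caffeine and similar instructions: done on arrival, before the learning phase; violations are noted and taken into the analysis.

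**3. Does the stated reason require unblinding?** The reason is module set-up. The module is web-based and contains the assigned material. If the tool can open a version from a code (an assumption; the article does not describe its functions), set-up needs no knowledge of the arm. The SAR reminder is the one element described as coming right before the task. Spoken by staff, it would reveal the SAR factor; shown on screen, it would not.

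**4. Reproducing the planned sample size.** Inputs from the Sample size calculation section: d = 0.40, two-sided alpha 0.05, power 0.80. For a factorial main effect (two cells against two cells):

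n per level = 2 × (1.960 + 0.842)² / 0.40² = 98.1, rounded up to 99, total 198.

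The exact t-test gives 100 per level, total 200. The 2 × 2 ANOVA F-test with 1 and 196 df has power 0.804 at N = 200. The stated 200 is reproduced, and the blinding point does not change it.

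**5. Illustration of size.** The article gives no experimenter-effect size, so b below is assumed. With no true effect and a spurious shift of b SD between 100 and 100, the non-centrality is b × √(100/2) = b × √50. The two-sided rejection rate is taken from the non-central t with 196 df.

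| Assumed shift b (SD) | As a share of d = 0.40 | Non-centrality | Type I error |
|---|---|---|---|
| 0 | 0 | 0 | 0.050 |
| 0.05 | one eighth | 0.35 | 0.064 |
| 0.10 | one quarter | 0.71 | 0.108 |
| 0.20 | one half | 1.41 | 0.291 |

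This is one between-group comparison of one outcome. The repeated stress outcomes are to be analysed with mixed models, so the figures show the order of size only.

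**The case against.** The strongest reply is that the plan already protects the outcomes well and discloses the one exception. Participants are blinded, SPs are not told the arm, and raters see videos in random order without the condition. The resources-demands differential is rated by the blinded participant, and the other three stress outcomes come from recordings or assays. Timing is fixed, control materials are matched in length, and participants sit quietly during the non-task recordings. The article does not say the tool can open modules by code, and if staff speak the SAR reminder, coding the module alone would not keep them blind. Who operates each step may be set out in the full protocol.

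Much of this stands, and it rules out three stronger readings:

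- A reader might infer that the same unblinded staff run all the stress measurements. That is plausible, because experimenters and SPs are the only session staff named, but the text does not say so.
- A reader might infer that only the video rating is protected by blinding. The Study design section contradicts this.
- A reader might infer that the stress outcomes as a whole are open to bias that could certainly be avoided. No experimenter is said to score any of them, behavioural compliance is checked before the learning phase, and full avoidance depends on how the reminder is delivered.

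The reply does not rescue the rationale. Fixed timing does not standardise tone or encouragement, the reminder can be put on screen, and data processing and validity decisions can be made blind whatever happens in the room.

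**Conclusion.** The concern holds in a limited form. The only reason given for unblinding does not by itself require it when the module is web-based. The exposure is confined to staff influence on arousal after the learning phase (CV3 to CV7, S3 to S6, Q3 to Q6) and to decisions on unusable cases that lead to replacement. The rated communication performance has its own protection through uninformed SPs and raters without knowledge of condition.

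The size is unknown. Under the assumed shifts of 0.05 to 0.20 SD, the type I error of a single main-effect test would be about 0.06 to 0.29 instead of 0.05. The lower end is nearly harmless. The upper end assumes a bias half as large as the planned effect, and nothing in the article shows that this would occur. The conclusion also assumes that the tool can open a module from a code, or can be changed to do so. No stated figure is wrong and N = 200 stands. The change is worth making because it is cheap, not because bias has been shown.

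**What to change.** **In the session.** Load the gender-stratified allocation into the web tool before use, so that a concealed participant code opens the assigned module and staff start every session in the same way. Show the SAR reminder on the participant's screen so that staff need not know the arm. Log any accidental unblinding.

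**In any case, including if sessions have begun.** Process the cardiovascular recordings and decide which cases are valid without knowledge of condition.

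**In the text.** Replace the sentence on experimenters in the Study design section accordingly. If experimenters stay unblinded, state who has contact with participants after the learning phase and who judges validity.

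**Cost.** A small change to the tool and the session script, with no added participants. An experimenter who must repair a module fault may learn the arm; the log covers that.

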**Fig. 1 Fig1:**
[figure not shown]
Flow of participants *Note*: SAR = Stress arousal reappraisal; WE = Worked example

### Study procedure

#### Online entry questionnaire

Interested students will be first invited to fill in an online entry questionnaire. The purpose of this questionnaire is to collect sociodemographic data as well as determine students’ eligibility. Eligible participants will then be scheduled for an individual experimental session in the research lab at the Institute for Medical Education in Bern.

#### Experimental session

The day before the experimental session, an email will be sent to the participants with the request to comply with the following instructions: no alcohol consumption and no intense physical activity 24 h before the session, no heavy meals and no caffeine consumption 2 h before the session, no smoking and no food consumption 1 h before the session.

The 2-hours session will start at 2pm for all participants to control for the psychophysiological effects of the circadian rhythm. The timing of each step will be identical across conditions (see Fig. 2).

Upon arrival at the lab, the experimental session, the cardiovascular measurement instruments, and the saliva sampling procedure will be explained to the participants, and written consent will be obtained from them. When explaining the experimental session, the experimenter will specifically mention that the BBN task will be video recorded, based on which participants’ performance will be rated. This information aims to increase participants’ task engagement. After these explanations, participants will have to verify their compliance with the behavioral instructions (food intake, caffeine consumption, etc.). Any violation of the behavioral instructions will be noted and considered in the statistical analysis. Participants will then be fitted with the sensors of the cardiovascular measurement devices (Finometer and VU-AMS). Next, a first saliva sample (S1) will be collected and a questionnaire (Q1; see Fig. 2 for details) answered, followed by a cardiovascular baseline measurement of 5 min (CV1). After the baseline measurement, participants will be informed about the setting of the upcoming task (i.e., BBN in prenatal setting). This will be followed by a cardiovascular recording of 2 min (CV2), a second saliva sample (S2), and a second questionnaire (Q2). During the next 40 min, participants will learn how to BBN with a web-based tool that includes a short introduction to BBN and the SPIKES protocol [1]. This protocol divides BBN into six stages (i.e., Setting, Perception, Invitation, Knowledge, Emotion, Strategy & Summary). The assigned intervention (SAR and/or WE) or control material will be part of this learning module. Immediately after the learning period, another saliva sample will be collected (S3), and a third questionnaire will be answered (Q3). Participants will then receive detailed information about a diagnosis (Trisomy 21) and be given 5 more minutes to prepare, before they have to deliver the bad news to an SP. For the BBN task, participants will be given a time limit of 12 min but will be allowed to finish earlier. Cardiovascular data will be recorded for 2 min before (CV3), during (CV4), and for 2 min after the BBN task (CV5). Next, another saliva sample will be collected (S4), and a fourth questionnaire will be answered (Q4). For the remainder of the experiment, there will be two blocks consisting in cardiovascular recording (CV6, CV7), followed by questionnaires (Q5, Q6) and saliva samples (S5, S6). During the cardiovascular recordings (excluding the BBN task), participants will be asked to sit quietly in an upright position, to not cross their legs, keep their eyes open, and their hands on the table.

**Fig. 2 Fig2:**
[figure not shown]
Experimental Session *Note*: Q1 contains the Multidimensional Mood State Questionnaire (MDMQ) and Stress Mindset Measure (SMM). Q2 contains the MDMQ, self-reported demands and resources, prior BBN experience and skills, and BBN interest and motivation. Q3 and Q4 both contain the MDMQ and self-reported demands and resources. Q5 includes the Depression, Anxiety and Stress Scale (DASS-21), Emotion Regulation Questionnaire (ERQ), SMM and MDMQ. Q6 contains the MDMQ

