Stress mindsets are global belief systems about the nature of stress [86]. Individuals with a stress-is-enhancing mindset belief that stress is positive and promotes health and performance, whereas individuals with a stress-is-debilitating mindset belief that stress is negative and harms health and performance. By assessing stress mindsets before and after the interventions, we can check if the manipulations affected an individual’s perception of stress (e.g., [57]). This is especially interesting for medical students, since they already have a certain understanding of the functionality of stress responses presented in SAR. Pre-existing stress mindsets might be pivotal for the effectiveness of SAR interventions [67]. One previous study suggests that most cognitive benefits occur when an individual holds a stress-is-enhancing mindset and appraises a stressor as challenge [57]. However, one could also argue that instructing individuals with a stress-is-enhancing mindset to reappraise stress arousal as functional is redundant [67]. Therefore, we will (1) consider stress mindset as a control variable in the primary analysis and (2) analyze stress mindset as a secondary outcome, to evaluate if SAR interventions affect the stress mindset of medical students.

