#### Depression, anxiety and stress

The DASS-21 [96, 97] measures the three emotional states depression, anxiety, and stress with 7 items each (total of 21 items). Participants indicate how each of the items applied to them over the past week. The scale ranges from 0 “Did not apply to me at all” to 3 “Applied to me very much or most of the time”. Scores are calculated for each of the three subscales. For each subscale, higher scores stand for a higher manifestation of the emotional state. The German version of the test possesses good psychometric properties [97]. Depression, anxiety, and stress will be treated as control variables.

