#### Emotion regulation

We will assess participants’ habitual use of the two emotion regulation strategies expressive suppression (4 items; e.g., “I keep my emotions to myself”) and cognitive reappraisal (6 items; e.g., “When I want to feel more positive emotion (such as joy or amusement), I change what I’m thinking about”) in their daily life with the German version of the ERQ [98]. Each item is rated on a scale ranging from 1 “not at all” to 7 “completely”. The mean is calculated separately for each emotion regulation strategy. Participants’ habitual use of expressive suppression and cognitive reappraisal will be used as control variables.

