### Statistical analysis plan

To test the effectiveness of the interventions on communication performance (H1.2, H2.2), we will use 2 (SAR vs. no SAR) x 2 (WE vs. no WE) between-subjects ANOVAs. For the analysis of the repeated psychophysiological stress response outcomes (H1.1, H2.1), we will use linear mixed models with the participants as random effect. To test if the effects of the interventions on communication performance are mediated by the psychophysiological stress response (H3.1, H3.2), we will conduct a bootstrapping mediation analysis following state-of-the-art methodology [101]. We will follow international guidelines to derive the parameters used in the statistical analysis. For each cardiovascular measure, the mean of each 1-minute period will be calculated. For salivary measures, the area under the curve with respect to ground and increase will be computed. Where sensible, we will transform skewed variables to approach normality. We will perform sensitivity analyses with the control variables gender, age, BMI, use of hormonal contraceptives, shift work, SP, stress mindset, depression anxiety and stress, body motion, BBN-related interest & motivation, BBN-related prior experience & skills, and habitual use of emotion regulation strategies. For significance testing, an alpha level of 0.05 will be used.

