### Possible pitfalls

We are aware that the present project is ambitious, which brings several possible challenges.

First, participation in the project will not be part of the regular medical study program but will rather be offered as an extracurricular learning opportunity. Although we assume that medical students have a general interest in communication training, we still rely on voluntary participation.

Second, medical students represent a distinct group of individuals compared to previous SAR-related research. In the third year, medical students already have a solid understanding of the functionality of their stress response, which is a core aspect of SAR interventions. Importantly, a person’s beliefs about stress (i.e., stress mindset) can affect their situation specific stress appraisal [67]. It remains to be seen how the SAR intervention applied in our study will affect the psychophysiology and performance of medical students specifically. We will investigate this issue by assessing participants’ stress mindset before and after the intervention and use it as control variable for primary analyses.

Third, there are more female medical students enrolled in Swiss universities than male students. Gender creates a possible confounder, given the different psychophysiology [87]. To ensure equal allocation to the experimental conditions, participants will therefore be stratified according to gender. Besides, the menstrual cycle of female participants causes monthly fluctuations of steroid hormones, which influence their psychophysiology. To control for these fluctuations, female participants will optimally be tested during the first week after menstruation. This puts restrictions on participation opportunities.

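### DASS-21 and ERQ are measured only after the interventions and the encounter but serve as control variables, so the adjusted sensitivity estimates may be biased; the role and time point of stress mindset are also not fixed

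*Protocol article*

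**What the plan says.** **Order of events.** Under Experimental session, the intervention sits in the 40-minute learning phase: "The assigned intervention (SAR and/or WE) or control material will be part of this learning module". Questionnaire Q3, the encounter and questionnaire Q4 follow. Only then comes the closing part of the session, which contains questionnaires Q5 and Q6.

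**Where the scales are.** The Fig. 2 note says "Q5 includes the Depression, Anxiety and Stress Scale (DASS-21), Emotion Regulation Questionnaire (ERQ), SMM and MDMQ". DASS-21 and ERQ appear in no other questionnaire in that note, and the section on the online entry questionnaire lists neither. The Stress Mindset Measure (SMM) is different: it is in questionnaire Q1, before the intervention, and again in Q5.

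**What the scales are for.** The section on depression, anxiety and stress states: "Depression, anxiety, and stress will be treated as control variables". The section on emotion regulation states that "habitual use of expressive suppression and cognitive reappraisal will be used as control variables". The Statistical analysis plan section specifies 2 x 2 ANOVAs and linear mixed models without naming covariates, and then says: "We will perform sensitivity analyses with the control variables gender, age, BMI, use of hormonal contraceptives, shift work, SP, stress mindset". That list goes on to include DASS-21, body motion and the emotion regulation strategies.

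**Stress mindset.** The Hypotheses section will "consider stress mindset as a control variable in the primary analysis and (2) analyze stress mindset as a secondary outcome". Possible pitfalls speaks of assessing participants' "stress mindset before and after the intervention and use it as control variable for primary analyses".

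**The concern.** A covariate in a randomised comparison should be fixed before the intervention can act on it. DASS-21 and ERQ, as scheduled, are not.

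- **ERQ cognitive reappraisal** is close in content to what SAR teaches. By questionnaire Q5 half the sample has seen the SAR screencast, reflected on past and future stressful situations, and been reminded just before the encounter to reappraise arousal.
- **DASS-21** covers the past week, which includes the session, and is answered soon after a task chosen because it is stressful. The answers may reflect how that task went.
- **Stress mindset** is a secondary outcome precisely because SAR may change it. The Q1 score is a sound covariate; the Q5 score would not be.

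Adjusting for a variable that the intervention or the outcome has moved no longer estimates the randomised effect. In a sensitivity analysis the practical risk is one of interpretation: a real effect shrinks after adjustment and is reported as not robust. The same reasoning applies to the worked example (WE) effect, and to body motion recorded during the encounter.

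**Working it through.** **1. The plan's own figure.** Sample size calculation gives d = 0.40, two-tailed alpha 0.05, power 0.80 and N = 200 (50 per cell). For a main effect, 100 against 100, the noncentrality is 0.40 x sqrt(200/4) = 2.83. With 196 degrees of freedom the power is 0.804, and the smallest sufficient N is 199. The stated N reproduces and is not in question.

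**2. Formula for the adjusted effect.** Take one covariate with within-arm correlation rho with the outcome, shifted by the intervention by delta SD:

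- adjusted difference = 0.40 - rho x delta
- share lost = rho x delta / 0.40
- for power, divide the adjusted difference by sqrt(1 - rho^2) x sqrt(1 + delta^2/4), and use N = 200 with 195 degrees of freedom.

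The document gives neither rho nor delta. The values below are assumptions, and the power refers to the adjusted model only.

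| rho | delta (SD) | adjusted effect | share lost | power, adjusted model | power, same covariate measured before the module |
|---|---|---|---|---|---|
| 0.1 | 0 | 0.40 | 0% | 0.81 | 0.81 |
| 0.1 | 0.5 | 0.35 | 12.5% | 0.67 | 0.81 |
| 0.3 | 0 | 0.40 | 0% | 0.84 | 0.84 |
| 0.3 | 0.1 | 0.37 | 7.5% | 0.78 | 0.84 |
| 0.3 | 0.2 | 0.34 | 15% | 0.70 | 0.84 |
| 0.3 | 0.3 | 0.31 | 22.5% | 0.62 | 0.84 |
| 0.3 | 0.5 | 0.25 | 37.5% | 0.43 | 0.84 |
| 0.5 | 0.5 | 0.15 | 62.5% | 0.22 | 0.90 |

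The last column shows the contrast: measured before the module, the same covariate leaves 0.40 intact and can only help precision.

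**3. Direction.** The product rho x delta can be negative. With rho = 0.3 and delta = -0.3 the adjusted effect is 0.40 + 0.09 = 0.49. Attenuation is plausible but not assured.

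**4. No direct effect on the scale is needed.** Suppose the answers only reflect the outcome, for instance how well the encounter went. Then delta = rho x 0.40, and the adjusted effect is 0.40 x (1 - rho^2): 0.40 x 0.91 = 0.364 at rho = 0.3, and 0.40 x 0.75 = 0.30 at rho = 0.5. This case applies to WE as much as to SAR.

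**5. Stress mindset, sections side by side.** Hypotheses and Possible pitfalls place it in the primary analysis; the Statistical analysis plan section places it among the sensitivity covariates. Hypotheses motivates the control role by pre-existing mindset, which points to the Q1 score. Possible pitfalls mentions both measurements and then the control role, without saying which score enters a model.

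**The case against.** Several stronger readings are tempting, and the document does not carry them.

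- **That the main hypothesis tests are biased or lose power.** The Statistical analysis plan section is the only one that specifies models. It names no covariates for the ANOVAs and mixed models, and confines the control variables to sensitivity analyses. On that reading the randomised comparison and its power of 0.80 stand.
- **That ERQ and DASS-21 are declared covariates of the primary analysis.** Their own sections call them control variables and no more. The general sentence under Experimental session measures, which mentions control variables in the primary analyses, sorts the measures by use and can mean analyses of the primary outcomes. Only stress mindset is placed in the primary analysis by name.
- **That the Q5 stress mindset score is a planned covariate.** No section says so. The Hypotheses section points to the baseline score; the wording in Possible pitfalls is ambiguous, not a commitment.
- **That the bias is certainly large.** ERQ asks about habits in daily life and DASS-21 about the past week. Nothing in the document shows that a 7-minute screencast moves either, and for DASS-21 and expressive suppression a mechanism specific to SAR is hard to name.

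All four points limit the reach and likely size of the problem. They do not remove it: the article commits to adjusting for scales collected after the intervention and the task, and later analysis wording cannot recover a baseline that was never collected.

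**Conclusion.** The point holds for the adjusted analyses. DASS-21 and ERQ are post-intervention measures used as covariates, and ERQ cognitive reappraisal is the most exposed. The adjusted SAR and WE estimates may be biased in either direction, plausibly towards zero. The size cannot be determined from the document: the loss runs from nothing to 62.5% of d = 0.40 over the assumed range, with the lower part more likely for scales of this kind. The illustration treats one covariate at a time, whereas the planned list is long. For stress mindset, the finding is an inconsistency about primary versus sensitivity analysis and an unstated time point. The sample size is unaffected.

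**What to change.** 1. Collect ERQ (10 items) and DASS-21 (21 items) before the learning module, preferably in the online entry questionnaire. Placing them in questionnaire Q1 would put 21 items on depression, anxiety and stress directly before the first cardiovascular baseline (CV1).
2. If the order cannot be changed, leave the Q5 scales out of all adjusted models.
3. State that only the Q1 stress mindset score is used as a covariate, and that the Q5 score is solely a secondary outcome.
4. Align the Hypotheses and Possible pitfalls sections with the Statistical analysis plan section, so that stress mindset has one role.
5. Report any model that adjusts for body motion during the encounter separately, and label it as adjusted for a post-randomisation variable.

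Cost: 31 existing items move to an earlier form, which becomes longer, and a few sentences change. The one measurement cost is that the past week in DASS-21 would then be the week of entry, not the week of the session.
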